# Medical devices

- Measurement of body composition

Body weight will be measured with a scale with the patient in underwear to an accuracy of ± 0.1 kg. Height will be measured with the patient barefoot to an accuracy of ± 0.1 cm. Circumferences will be measured with a seamstress’ tape measure. Waistline is the smallest circumference at the height of the umbilicus and hip circumference is the largest circumference opposite the femoral heads. These methods are standardised in the CRNH and are performed by the same investigator.

Body composition will be measured by dual energy X-ray absorptiometry (DEXA). This method is usually used for measurement of bone mineral density. It is based on body scanning with an X-ray beam at 2 different levels, which make it possible to individualise 3 compartments: mineral mass, active tissue mass and fatty mass. This method that uses little radiation (less than that of one conventional chest X-ray) is used in adults, as well as in children and now is considered as the reference method to measure body compartments precisely. For this examination, the subject is supine on a table, in his or her underwear. The total duration of the study is about 10 minutes.

- Fasting blood sample collection

In the morning, fasting (an 8 hour fast), volunteers will undergo blood sample collection of about 40 ml which immediately will be centrifuged, divided into aliquots and frozen for analysis of substrates and hormones. We will measure the circulating levels of the following:

- glucose and insulin
- lipids: cholesterol, triglycerides, free fatty acids (FFA) and high and low density lipoproteins (HDL and LDL- cholesterol)
- leptin and adiponectin
- inflammatory factors: CRPus and IL6.

About 7 ml of blood will be collected to obtain plasma or serum which will be stored in order to perform additional assay measurements regarding results of previous measurements.

All sera intended for assay measurement of signals of adiposity and of inflammatory factors will be analysed in the INSERM Unit U872 (Eq 7). The serum collection will be stored by the Inserm Unit U872 (Eq. 7). Total blood volume collected in four times of visits therefore will be about 160 mL for the totality of the study. Blood samples will be stored at -80 °C up until the end of the study, and then will be destroyed.

- Sampling of peri-umbilical adipose tissue

A sample of adipose tissue of about 500 mg will be collected by needle puncture suctioning performed on volunteers. This sample, collected by the investigator, is performed in routine practice in the department of nutrition of Pitié Salpetrière Hospital to measure cell size. After local anaesthesia with 2 ml of 1% xylocaine without isoprenaline, the peri-umbilical adipose tissue will be collected by a small calibre needle with suctioning to follow the outcome of the population and morphology. For each adipose tissue sample collected (subcutaneous), cell size will be evaluated before and after treatment.

Investigational studies for investigation of adipose tissue (inflammatory status, insulin sensitivity) in vitro in culture will be performed by the AdipoPhyt firm.

- Specific instructions during the investigational period

Persons who are subjects in the study must not change their dietary habits. Lastly, any form of medical therapy initiated during the investigational period must be reported by the volunteer.

# Collection of human biological samples

- Description of type of samples:

Blood samples and adipose tissue.

- Description of conditions for sampling:

Blood samples will be collected at D-1 to -14, D0, D 120 and D180 after 8 hours of fasting, between 8 and 9:30 am. Test tubes collected will be kept at 4 °C starting with collection of the sample, centrifuged to 4 °C, divided into aliquots and stored at -80 °C until their use for the planned analyses.

The sample of adipose tissue will be collected after application of local anaesthesia with 2 ml of 1% xylocaine without isoprenaline, peri-umbilical adipose tissue sample will be collected by suctioning with a fine needle to measure the adipocyte size immediately and to conduct study of cell culture in vitro.

Blood samples will be stored by INSERM U872 (Eq7) at -80 °C up until end of study (last analysis of last patient included), and then they will be destroyed. Those of peri-umbilical adipose tissue will be stored at -80 °C by ADIPOPHYT up until end of study (last analysis of last patient included), and then they will be destroyed.

# study safety

## DEFINITIONS RELATING TO SAFETY

See article R. 1123-39 no. 1; no. 2; no. 6; and no. 8 of PHC

Adverse event

Any harmful event occurring in a person who is a subject in a biomedical research study whether this occurrence is related to the study or not or to a product on which the study is focused.

Adverse effect

Any adverse event related to the study.

For each adverse event, the investigator and the sponsor evaluate its causal relation with the study. Any adverse event considered by the investigator or by the sponsor as having a scientifically reasonable causal relation with the study is qualified as an adverse effect. The expression “scientifically reasonable causal relation”, generally means that evidence or an argument exists enabling to suggest, scientifically, a cause-to-effect relationship between the harmful and unwanted reaction and the study (i.e. procedure, method, action or product which is the subject of the study). An adverse event due to the study can be related, for example, to the procedures, methods, to the procedures performed or to the products which are the subject of the study or used for requirements of the study.

Serious adverse event or effect

Any adverse event or effect which meets the definition of “serious” if:

- it results in death;

- is life-threatening for the person who is the subject of the study;

- requires hospitalisation or results in prolongation of hospitalisation;

- causes important or durable incapacity or disability;

- is translated by a congenital anomaly or malformation.

For each event/ adverse effect, the investigator and sponsor evaluate its causal relationship.

The term “life-threatening” corresponds to an event/effect which is immediately life-threatening for the person who is a subject in the study at time of the adverse event and not an event/effect which could possibly have caused death if it had been more severe. Medical judgement must be exercised to determine if the adverse event or effect is serious in other cases. Major adverse effects or events which are not immediately life-threatening or which do not result in death or in hospitalisation, but which can place a subject in danger or require an intervention to prevent its progression to one of the aforementioned criterion must also be considered as serious.

Unexpected serious adverse event

An unexpected adverse event means any adverse event whose nature, severity or outcome do not coincide with information relating to products, procedures performed and methods used during the study.

For each adverse event, the sponsor must evaluate if it is unexpected or not.

Evaluation of the unexpected feature of an adverse event is done based on information described in the study protocol or in the investigator brochure, in particular, if applicable, relating to procedures and method performed during the study or to products which are subject of the study or used for requirements of the study.

## investigators’ role

### Evaluation of severity/causal relation of adverse events

The investigator must evaluate the following for each adverse event collected during the study:

- its seriousness,

- its causal relation between the serious adverse event and the study, and then send the result of his or her evaluation to the sponsor.

Notification of serious adverse events to the sponsor

The investigator will notify without delay starting from day when he/she became aware of it all SAE which occurred during the study:

Using the SAE reporting form that he/she will send by fax and by e-mail to the sponsor at [name] . Att. [name] [name]

In this notification, the investigator sends the sponsor his/her evaluation of the causal relation of the serious adverse event with the study (that is, with the procedure, method, procedure or product that is the subject of the study).

The investigator will also provide all information necessary for medical evaluation of the observation to the sponsor (laboratory test reports, pathology report, and radiology report).

The sponsor can request further information from the investigator.

All documents sent by the investigator must be made anonymous.

SAE occurring after the study must be notified to the sponsor and followed up until their final resolution.

**Notification of adverse events to the sponsor**

The investigator will complete an adverse event form for all adverse events that occurred during the study. Such events will be recorded in a dedicated Excel spreadsheet at the study site. The CRA will retrieve pages as monitoring visits are completed and will send a copy of them to the safety unit upon his/her return from the monitoring visit. A copy of the updated Excel spreadsheet will also be sent to the Sponsor. If analysis of cases results in an SAE, he/she must follow the procedure for notification and follow-up of SAEs described in the aforementioned..

## sponsor’s role

The sponsor must report all suspect serious adverse events related to the product or to the study to the CPP Ile-de-France VI and to AFSSAPS without delay and at latest with an initial time of 7 calendar days starting from when he/she became aware of it for serious adverse events which resulted in death or where life-threatening and within 15 days for other serious adverse events. Any initial report will be completed by a follow-up report delaying relevant further information concerning serious adverse events within a time period of 8 days starting from the abovementioned deadlines.

The sponsor will make a decision based on significance of the serious adverse events that he/she reports and the consequences that he/she draws, in particular, concerning conduct of the study.

The sponsor will also make a decision on the causal relation of the adverse event using a joint analysis with the team from PiLeJe safety staff. The unexpected feature will be established by the sponsor based on nutritional safety data from Pileje concerning the studied product and also the scientific and medical literature concerning the component ingredients of the product.

The sponsor will keep up-to-date detailed registries of all adverse events (AE, SAE, USAE)

The sponsor will periodically report to AFSSAPS, as well as to the CPP:

- Each semester:
- a list of suspect unexpected SAE that occurred in other trials conducted in France with the same product, procedure or method
- a concise synthesis underlining the principle problems of safety raised.
- Yearly:
- an annual safety report taking into account all available safety information.

The sponsor keeps up-to-date detailed registries of all adverse events notified to his/her by investigators.

## follow-up of patients in case of a serious adverse event

Follow-up of patients who have had a serious adverse event will be performed by the doctor responsible for the study.

## Independent monitoring committee

There is no monitoring committee because this is not necessary considering the type of product under study: the risk is almost non-existent because it is a combination of known dietary ingredients already used in other formulations of dietary supplements marketed by the Pileje group (OligobianeCr (launched on the market in early 2001) and Multibiane Age Protect (launched on the market in March 2008) for Guanylor®-Cr and Glycabiane (launched on the market in March 2008) for the combination Glycabiane and nutrivigilance safety is free of any adverse event.

# Data collection and processing

## data collection

Data in the form of questionnaires will be collected in case report forms by investigators mandated in this study. Data concerning biological samples from patients will be inserted in the medical dossier of the person who is a subject in the study. An anonymised copy will be inserted in the CRF in a plastic folder provided for this purpose.

## Description of channel of data management before data processing

Data are stored in locking cabinets on-site.

## Data collection

Data will be collected in compliance with confidentiality of the identity of persons participating in this study and all personal or medical information concerning them. Patients’ anonymity will be ensured by inserting at most the first 3 letters of the patient’s surname and the first 2 letters of his first name on all documents necessary for this study or by erasure by appropriate means (white correction marker, correcting fluid, etc.) of data associated with a name in copies of source documents, intended for documentation of the study.

Clinical data will be reported or results will be stapled in the case report forms using data from the database after they are made anonymous.

Data collection will be performed by means of case report forms specific for the study. Each dossier will be completed progressively as information is collected. If data are missing, the latter will be indicated by the sign “MD” (missing data). If there are data not applicable to the subject included in the study, such data will be annotated with the term “NA” (not applicable). If corrections must be made to the case report form, the erroneous data must be crossed out with a single line (without concealing the original entry), the new data must be written next to it with the investigator’s initials and date on which the correction was made. Investigators will sign pages of the CRF corresponding to their examination.

Subjects will have the right of access to source data and documents through the study investigators. Data will be archived confidentially for a period of 15 years after the end of the study. Healthy volunteers, in compliance with legislation, will also be informed of the overall results of the study.

Data will be stored in locking cabinets on-site.

## Computerised data processing

Data are digitised in single entry with double reading. This will be done under the responsibility of [name], co-investigator of the study, who validates data after each entry. Data is entered in an Excel spreadsheet where each page corresponds to a type of parameter. A summary page makes it possible to record all data on a single page, which enables it to be transferred to the statistical utilisation software (SAS).

- Traceability will be ensured by an attached table. Each change will be noted, dated, and listing the reason and the author of this change.

− Data will be kept in a computer located on [name]’s desk; this computer is on the secure network of the Pité Salpêtrière hospital, a hospital of the APHP[[4]](#footnote-5), protected with a specific ID and password.

− Weekly saving on to a computer data stick dedicated to the study, as well as saving of “paper” documents will also be performed in the laboratory. All these data will be stored in a locking file cabinet.

− Similarly, procedures, names, addresses, phone and fax numbers and e-mails of doctors participating in this study and reports of meetings of the steering committee and of follow-up of study will be kept in a room and a locking cabinet. Access will be controlled and restricted to a list of participants established by the scientific person responsible.

- Lastly, all these data will be transferred to the server for saving in Unit U872 (team 7) which is protected according to rules in force in INSERM.

Confidentiality relating to each volunteer participating in this study is assured. Clinical data and source data will be accessed directly in case of an audit ordered by the sponsor or an inspection conducted by the competent administrative authorities.

# Statistical analysis of data

## Number of subjects necessary

Based on the literature, a 10% decrease in fasting glycaemia can be expected in the Glycabiane group compared to the Control group, after 4 months of supplementation. The statistical hypothesis is a 10% difference in the primary evaluation end point (Fasting glycaemia) between subjects who received the placebo and those who received Glycabiane®. Therefore, the number of subjects to be enrolled in this trial, with an alpha risk of 5% and a power of 90%, is 25 per group, i.e. a total of 50 subjects. 60 subjects will be screened in the study to ensure inclusion and follow-up of a total of 50 patients.

**Statistical considerations**

All data will be listed by group and by subject.

Descriptive statistics will be compiled by type of parameter analysed:

- Quantitative variable: sample size, mean, standard deviation, minimum and maximum of raw data and, if necessary, changes compared to baseline, as well as percent change.
- Qualitative variable: sample size, absolute frequency (N) and relative frequency (%) by class.

Descriptive statistics will be compiled by group.

Graphs will be provided according to type of variable:

Quantitative variable: Representation by group of the mean +/- SEM during visits.

Qualitative variable: Representation by group of percentages by class

Changes to clinical and biological parameters will be analysed for each subject before and during kinetic follow-up. Manova and Anova kinetic tests will be used. We will relate clinical, biological parameters, morphological data and data expression by logistic regression analysis. INSERM U872 (Eq7) over the last few years has gained expertise in analysis of these data (use of JMP software (derived from SAS software). For quantitative data, repeated measures analysis of variance will be used (Anova, Manova, logistic regression model). Statistical tests will be performed with an alpha risk of concluding in an erroneous difference set at 5%.

Statistical analysis will be performed by INSERM U872 (Eq7).

Description of sample

A description of subjects not included, subjects included who completed the study and of subjects included who withdrew from the study before its completion will be presented with a table of absolute frequency (N) and relative frequency (%).

Reasons for withdrawals will be presented in a listing.

A description of subjects at baseline, that is, before use of the studied product, will be reported by descriptive statistics on available demographic data (age, sex, height, weight and BMI).

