Recently, a team led by Salomon evaluated the effect of ingestion of 3 g of cinnamon per day during 14 days on glucose tolerance and sensitivity to insulin in 8 healthy men 25 ± 1 years of age with a BMI of 24± 0.7. 14 subjects received either Placebo or cinnamon extract alternately during 14 days. Supplementation with Placebo was continued for 5 days after the 14 days’ supplementation. Glucose tolerance tests were conducted at D0, D1, D14, D16, D18 and D20. Ingestion of cinnamon significantly reduced glycaemic response to the glucose tolerance test at D1 (-13.1±6.3% vs. D0, p<0.05) and D14 (-5.5±8.1% vs. D0, p=0.09). Ingestion of cinnamon also reduced the insulin response at D14 (-27.1±6.2% vs. D0, p <0.05) and sensitivity to insulin (p<0.05 at D14 vs. D0). These positive effects ceased after discontinuation of supplementation suggesting that cinnamon can improve glycaemic control and sensitivity to insulin, but that these effects are reversible (28). Lastly, another study on 15 healthy subjects showed a beneficial effect of ingestion of 3 g of cinnamon mixed with rice cake on postprandial serum insulin (vs. rice cake without cinnamon). No effect was found with 1 g of cinnamon and no effect was found on glycaemia (29).

In conclusion, convincing scientific data are still lacking to conclude in an effect of cinnamon on glycaemia, although it seems that cinnamon has a slight hypoglycaemia-inducing effect. Regarding levels of HbA1c, the effect on this parameter appears negligible, but other randomised placebo-controlled clinical studies are necessary to evaluate its real impact.

| **Bibliographical References** | **Study design and number of subjects (N)** | **Target population** | **Intervention** | **Results** | **Comments** |
| --- | --- | --- | --- | --- | --- |

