**Primary analysis**

The primary evaluation end point will be the fasting glycaemia before and after supplementation. It will be compared within groups and between the two groups using a test of comparison of means.

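### Logistic regression is prescribed for continuous data with no binary outcome defined, and the general repeated-measures rule does not exempt fasting glycaemia or separate D120 from the off-product visit

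*Protocol*

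**What the plan says.** Section XIII of the protocol, under Statistical considerations, sets a general rule: "For quantitative data, repeated measures analysis of variance will be used (Anova, Manova, logistic regression model". Just before it, the same paragraph says "We will relate clinical, biological parameters, morphological data and data expression by logistic regression analysis". On timing it says only "Changes to clinical and biological parameters will be analysed for each subject before and during kinetic follow-up". It lists no visits, names no effect to be tested and does not set the primary endpoint apart.

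The next subsection, Primary analysis, is specific: "The primary evaluation end point will be the fasting glycaemia before and after supplementation", and "It will be compared within groups and between the two groups using a test of comparison of means".

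Section X gives the sampling times: "Blood samples will be collected at D-1 to -14, D0, D 120 and D180 after 8 hours of fasting". The study flowchart agrees that glycaemia is not measured at the two-month visit. D180 (V5) falls two months after supplementation ends. The sample-size text places the expected 10% between-group difference after 4 months of supplementation.

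**The concern.** There are two separate problems.

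**Logistic regression.** It models a categorical, usually binary, outcome. It is not a form of repeated-measures analysis of variance, and it does not describe relations among continuous variables. The parameters concerned (HbA1c, lipids, insulin, IL-6, adipocyte size and the like) are essentially continuous. To follow the text, the analyst would have to choose cut-points that the protocol does not give, possibly after seeing the data.

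**Fasting glycaemia.** It is quantitative, so the general rule covers it, while Primary analysis gives it a comparison of means. Nothing states which governs. The choice can matter because the only glycaemia value after baseline other than D120 is taken off product. A result that averages the two visits would answer a different question from the one the trial was sized on.

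**Working it through.** **1. Logistic regression.** No arithmetic applies. The sentences that prescribe it can be set beside the endpoint lists in Secondary objectives, Secondary endpoints and Secondary analyses. None of these lists defines a binary response. The method is named twice, once for quantitative data and once for associations, and has no stated outcome either time.

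**2. What the sample size rests on.** Inputs from the protocol: SD 0.13 g/L, a 10% difference, alpha 5%, power 90%. Two assumptions are needed: a two-sided test, and a baseline mean, ranged over the eligibility window of 1.00 to 1.26 g/L.

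n per group = 2 × [0.13 × (1.960 + 1.282) / δ]², with δ = 0.10 × baseline.

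| Baseline (g/L) | δ (g/L) | n per group |
|---|---|---|
| 1.00 | 0.100 | 36 |
| 1.13 | 0.113 | 28 |
| 1.163 | 0.1163 | 27 |
| 1.20 | 0.120 | 25 |
| 1.26 | 0.126 | 23 |

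The stated 25 is met at a baseline of 1.20 g/L. It is what a two-group comparison of means at one time point gives, which matches Primary analysis.

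**3. What averaging in D180 would do.** Assume a baseline at the middle of the window, 1.13 g/L, so d = 0.113 / 0.13 = 0.87. Assume 25 per group, equal variances, and a common correlation ρ of 0.3, 0.5 or 0.7 between visits. Let f be the fraction of the D120 effect still present at D180. Power is two-sided from the noncentral t with 48 degrees of freedom.

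- D120 alone: effect d = 0.87, power 85%.
- Average of D120 and D180: standardised effect = [d(1 + f)/2] / √[(1 + ρ)/2].
  - f = 0: effects 0.54, 0.50 and 0.47; power 46%, 41% and 37%.
  - f = 0.5: effects 0.81, 0.75 and 0.71; power 80%, 74% and 69%.
  - f = 1: effects 1.08, 1.01 and 0.94; power 96%, 94% and 90%.
- Group-by-time test on the changes from D0 to D120 and to D180 (Hotelling, F with 2 and 47 degrees of freedom), f = 0: power 74%, 88% and 98%.

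**4. Sensitivity.** Take δ = 0.12 g/L (the baseline that reproduces 25) and a normal approximation. The D120 comparison has power 90%. The post-baseline average minus D0 has 36%, 47% and 68% at f = 0, and 67%, 81% and 95% at f = 0.5. The pattern is the same.

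**5. When the two sections agree.** With D0 and D120 only, the group-by-time F equals the square of the t statistic on change (10.967 both ways in a simulated data set). The two rules can therefore differ in substance only once D180 enters.

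**The case against.** The strongest reply is that Primary analysis is the specific section and ordinarily overrides a general paragraph. It ties the endpoint to before and after supplementation, and the sample size is set at 4 months. Analysis of variance is itself a comparison of means, and on two time points it reproduces the t-test on change. This stands: the protocol has a dedicated primary analysis, and the fault is an unstated precedence, not a flat contradiction.

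Several stronger readings are tempting but not supported:

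- **That D180 is mixed into the primary test.** No sentence says D180 enters any model. It would have to enter only if more than one post-baseline glycaemia value were modelled.
- **That a group main effect over D0, D120 and D180 is planned, with power of 20-28%.** The protocol names no such effect. Its wording about changes over time points rather to time or group-by-time effects, and a group-by-time test is not diluted in that way.
- **That the protocol holds the effect to be gone by D180.** Its summary of one cited study reads "suggesting that cinnamon can improve glycaemic control and sensitivity to insulin, but that these effects are reversible". That was a 14-day study of cinnamon alone in 8 healthy men. Its literature table also describes a type 2 diabetes study in which glucose rose slightly after stopping but stayed below baseline. Zero carryover is an assumption.
- **That subjects missing V5 lose their V4 data.** The protocol states no complete-case rule, and missing-data handling may properly sit in an analysis plan that is not shown.
- **That variables will be split at the median.** No cut-point is stated. The protocol also foresees qualitative variables, for which logistic regression could be legitimate once an outcome is named.

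**Conclusion.** The point holds in a limited form. Naming logistic regression for quantitative data, and for relating essentially continuous parameters, is an error in the text as written. It bears on general and association analyses and leaves the comparison of means in Primary analysis intact.

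The overlap between the general repeated-measures rule and Primary analysis is an ambiguity worth closing, because the only further post-baseline glycaemia value is off product. The possible cost is conditional. Power would be about 37-46% instead of 85% if a D120/D180 average were used and nothing of the effect remained, 69-80% if half remained, and no loss if all of it remained. These figures rest on assumed values for the baseline mean, the correlation and the carryover. Moderate severity is appropriate: it should be corrected, but it does not undermine the design.

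**What to change.** 1. State that the primary result is the between-group contrast in fasting glycaemia at D120 (V4), adjusted for the D0 value, and that this takes precedence over the general paragraph.
2. For endpoints measured at several visits, report the D120 contrast from a repeated-measures model with group-by-visit terms that uses all available data. Report D180 as a separate off-product contrast.
3. Remove logistic regression from the sentence on quantitative data. For relating continuous parameters, use linear regression or rank correlation; if logistic regression is kept, define its binary outcome in advance.

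The cost is about three sentences of wording and standard software procedures. The sample size, visits and measurements do not change.
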